#### Objective 2: External Validation of the Model

The model accuracy will then be assessed externally using the RSC Practice network data to verify the specificity of the model predictions, as well as the sensitivity, negative predictive value, and positive predictive value [16,17].

#### Objective 3: Analysis of Additional Datasets

A separate RECAP-V1 model will be developed, using the same methodology as described in Objective 1, for the CCAS and DoctalyHealth datasets, and the models will be internally validated following the same procedure as used in building the model for the iCare dataset.

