**Methods:**

After the data have been collected, we will assess the degree of missingness and use a combination of traditional data imputation using multiple imputation by chained equations, as well as more novel machine-learning approaches to impute the missing data for the final analysis. For predictive model development, we will use multiple logistic regression analyses to construct the model. We aim to recruit a minimum of 1317 patients for model development and validation. We will then externally validate the model on an independent dataset of 1400 patients. The model will also be applied for multiple different datasets to assess both its performance in different patient groups and its applicability for different methods of data collection.

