### Study Objectives

The primary objective of the study is the development of a data-driven risk tool (RECAP-V1) for use in general practitioner (GP)-patient consultations (mainly by phone or video) in the context of COVID-19. As a secondary objective, the early warning risk tool will be externally validated on an independent dataset. As a third objective, the performance of the model in additional datasets will be assessed. Data for both model development and model validation will be prospectively collected.

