### Definition of Analysis Population

The primary population set is patients presenting with clinically diagnosed COVID-19 in general practices and requiring assessment for the risk of clinical deterioration. The primary RECAP-V1 model will be built using data from iCare and externally validated using data from the RSC Practice network.

Additional population sets are patients that are part of DoctalyHealth, as well as patients who are being assessed by the NHS111 CCAS. Based on clinical expertise, the patients who are being assessed as part of NHS111 CCAS are expected to be experiencing more severe symptoms of COVID-19. Similarly, for DoctalyHealth, the data are collected from a home monitoring system; hence, we are expecting this patient population to be different from the iCare and RSC Practice network populations. Moreover, some of the important clinical parameters such as oxygen saturation or rate of breathing may be missing for DoctalyHealth.

A separate RECAP model will be built for the CCAS patients and the DoctalyHealth patients.

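### Objective 3 promises to assess the RECAP-V1 model in further datasets, but its method builds separate models there; the iCare equation goes untested in DoctalyHealth and is only indirectly explored in CCAS

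*SAP article*

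**What the plan says.** Two places in the SAP article describe the aim. Study Objectives has "As a third objective, the performance of the model in additional datasets will be assessed". The Methods part of the abstract has "The model will also be applied for multiple different datasets to assess both its performance in different patient groups and its applicability" and extends this to different ways of collecting data. In both, the model meant is the RECAP-V1 tool of the primary objective.

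Definition of Analysis Population identifies the further datasets: "Additional population sets are patients that are part of DoctalyHealth, as well as patients who are being assessed by the NHS111 CCAS". It then says "A separate RECAP model will be built for the CCAS patients and the DoctalyHealth patients".

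The section Objective 3: Analysis of Additional Datasets gives the method: "A separate RECAP-V1 model will be developed, using the same methodology as described in Objective 1, for the CCAS and DoctalyHealth datasets". Validation of what is built there is internal only, by the bootstrap procedure set out for iCare. The Results section likewise assigns the DoctalyHealth data to developing a model for that group.

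External validation of the iCare model is placed in one dataset only: "The primary RECAP-V1 model will be built using data from iCare and externally validated using data from the RSC Practice network". Objective 2 repeats this.

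The last paragraph of Exploratory Analyses adds that the authors will explore pooling CCAS with iCare, quantify how the patients differ, and use internal-external cross-validation by source dataset to look at transferability. DoctalyHealth is not part of that step.

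**The concern.** Assessing a model in a new population means carrying its coefficients and thresholds over unchanged and comparing predictions with outcomes. Redeveloping a model in the new data answers another question: how well a model tailored to those data can do. The objective asks the first question and the method answers the second.

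The separate models could differ a good deal from the iCare model. Following Objective 1 means fresh fractional polynomials, fresh backward elimination at P<.05 and new cut-offs chosen by inspecting each ROC curve. The Missing Data section also drops any predictor more than 50% missing. Objective 3 nevertheless calls the result RECAP-V1, so different equations with different thresholds could share one name and the same colour labels. The section also moves from a single model to models in the plural, which leaves the number of equations unclear.

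At stake is whether the study can report on its third objective. The plan itself expects CCAS patients to be more severely ill and DoctalyHealth patients to differ from the general-practice cohorts. In such groups calibration and cut-offs are the most likely to shift, so a performance check is most informative there.

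**Working it through.** This is mainly a question of consistency, so the first step sets the sections side by side.

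| Dataset | Final iCare equation and cut-offs applied? | Where stated |
|---|---|---|
| RSC network | Planned as the external validation | Definition of Analysis Population; Objective 2 |
| CCAS | Not under Objective 3; exploratory cross-validation with iCare by source, final equation and cut-offs not specified | Objective 3; Exploratory Analyses |
| DoctalyHealth | Not planned anywhere | Objective 3; Results |

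**Inputs (Results section).** iCare 2429, RSC 1303, CCAS 2088, DoctalyHealth approximately 5000.

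**Reproducing the plan's figure.** 2429 + 1303 = 3732, as stated for the combined sample.

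**Size.**
- Additional datasets: 2088 + 5000 = about 7088.
- All patients outside the development set: 7088 + 1303 = about 8391.
- No check of the iCare model (DoctalyHealth): 5000 / 8391 = 0.596, about 60%. Within the two additional datasets: 5000 / 7088 = 0.705, about 71%.
- Indirect exploratory check only (CCAS): 2088 / 8391 = 0.249, about 25%. Within the two additional datasets: 2088 / 7088 = 0.295, about 29%.

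**What the exploratory step delivers for CCAS.** With two sources, internal-external cross-validation fits in one and tests in the other. The round that fits in iCare and tests in CCAS comes close to what Objective 3 promises. The plan does not say that this round uses the final selected predictors and coefficients, or that the red/amber/green cut-offs are carried over. Its stated purpose is to gain power from a combined model.

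**Would the missing analysis be informative?** The document gives no admission rate for these datasets. Assuming its general 10%:
- CCAS: 2088 × 0.10 = about 209 admissions; DoctalyHealth: 5000 × 0.10 = 500.
- At assumed rates of 5% to 20%: about 104 to 418 in CCAS and 250 to 1000 in DoctalyHealth.
- 95% CI half-width for specificity at the plan's assumed 87%: 1.96 × √(0.87 × 0.13 / (0.9 × n)). CCAS: 1.96 × √(0.1131 / 1879.2) = 0.015. DoctalyHealth: 1.96 × √(0.1131 / 4500) = 0.010. Both are well inside the 0.05 precision the plan sets for external validation.

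These figures assume that every patient has the predictors needed. That may fail in DoctalyHealth.

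**The case against.** A reader might infer that transportability is never measured in any of the roughly 7088 patients, 84% of those outside the development set. The document does not support that. The exploratory cross-validation bears on transferability between iCare and CCAS, so the 2088 CCAS patients cannot be counted as contributing nothing. Only DoctalyHealth is left with no check.

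A reader might also infer that separate models are a mistake. They are a reasoned choice: Definition of Analysis Population expects the two groups to differ from the general-practice cohorts and warns that oxygen saturation or breathing rate may be missing in DoctalyHealth. If so, the full iCare equation may not be computable there. This justifies adding separate models, but it does not meet the objective as worded. It also limits the remedy, because a reduced model tested in DoctalyHealth is not the full RECAP-V1 equation.

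A third inference is that the plan would put the iCare equation into use in CCAS or DoctalyHealth without testing it. No section states that intention. Study Objectives describes a tool for GP consultations, and RSC is the matching validation setting. The abstract's Objective is broader, covering anyone with suspected COVID-19, but that wording does not establish the intention.

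It is fair to add that internal validation alone is an openly stated limitation of the new models, not an error, and that the shared name is an editorial matter: elsewhere the plan does distinguish the primary RECAP-V1 model from a separate RECAP model.

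**Conclusion.** The mismatch stands. The abstract and Study Objectives promise the performance of the RECAP-V1 model in additional datasets; Definition of Analysis Population and Objective 3 plan separate, internally validated models in those datasets. This is not an effect of condensing a longer plan, because the article states both the aim and a method that does not serve it.

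As written, the iCare equation and its cut-offs are not tested in DoctalyHealth (about 5000 patients). In CCAS (2088 patients) they are approached only through an exploratory step that does not specify evaluating them. The conclusion rests on reading the model in the third objective as the RECAP-V1 tool of the primary objective; the abstract, which speaks of applying that model to other datasets, supports this. The patient counts are those of May 10, 2021, and the DoctalyHealth figure is approximate. The point should be resolved before analysis, but it does not affect the primary development or the RSC validation.

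**What to change.** In Objective 3, before the separate models are developed, add a step that applies the frozen iCare model and its cut-offs to CCAS and to DoctalyHealth. Report discrimination, calibration intercept and slope, sensitivity, specificity, positive and negative predictive values, and observed risk in each colour category.

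Where oxygen saturation or respiratory rate is absent, apply a reduced model fitted in iCare, of the kind already foreseen under Exploratory Analyses. Report the result as a test of that reduced model, not of the full RECAP-V1 equation.

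Keep the separate CCAS and DoctalyHealth models as a further step, state how many there will be, and give each a name distinct from RECAP-V1.

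If the frozen model will not be applied, reword the abstract and Study Objectives to say that separate models are developed and that the iCare model's performance in these populations is not assessed under Objective 3.

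The cost is SAP wording and a modest additional analysis of data already collected, including handling of missing predictors. For DoctalyHealth it may turn out that only the reduced model can be tested. Rewording alone costs almost nothing but gives up the third objective as now stated.

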#### Subgroup Analysis

The performance of the model will be investigated in specific groups of patients, focusing primarily on gender and age (<65 years).

#### Missing Data

The extent of missing data for each variable (outcome and predictors) will be assessed among all patients. Particular note will be taken of the potential for missing data in the oxygen saturation and temperature fields (in case the patient does not have instruments to measure these), and for respiratory rate (difficult to estimate unless independently counted visually) as these are considered particularly important factors for outcome.

If model outcome data are missing for >5% of the patients, methods to deal with missing data will be used and a sensitivity analysis to estimate the effect of using these methods will be carried out by comparing the estimated risk obtained without implementing a missing data method and the risk estimated using missing data methods.

The degree of missingness in predictor variables will be assessed. If the degree of missingness is above 50% for any predictor variable, then that predictor variable will be excluded from the model. If the degree of missingness is less than 50%, the data will be imputed using multiple imputation chain equations [18]. A total of 5 imputations will be performed and aggregated based on Rubin’s rules [19].

Data missingness mechanisms will be investigated to ascertain if the data are missing completely at random, at random, or not at random. This will be performed by considering the data structure to understand the dependency relationships between the missing data and the observed data. The missing data will then be described in relation to the degrees of missingness, missing data patterns, and possible reasons for missingness. We will also compare the characteristics of the patients with missing data and patients with complete data entries, which will allow us to assess the plausibility of the data missing completely at random. The distributions of the continuous predictor variables will be investigated for normality. Any missing continuous data that are not distributed normally will be transformed to a normal distribution for imputation and transformed back to the original scale for the final analysis.

Multiple imputation chain equations [18,20] will be used, and all of the predictor variables (with less than 50% missing data) will be included in the imputation model. Variables without missing data will also be included, and the outcome variable (hospital admission) will be used for imputation of the predictor variables. We will use linear regression for continuous variables (normally distributed or transformed), and logit or ordinal logit regression for categorical variables. We will compare observed and imputed values, especially for variables for which the fraction of missing data is large [21].

The same imputation methods will be used in all datasets, for both continuous and categorical variables.

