### Sample Size

#### Model Development and Internal Validation

Assuming that 10% of patients diagnosed with COVID-19 will be admitted to hospital [6], a 0.05 acceptable difference in apparent and adjusted Cox-Snell R-squared, 0.05 margin of error in estimation of the intercept, a binary outcome based on admission to hospital, and a maximum of 24 predictor parameters [5], we estimate that the minimum sample size required for new model development is 1317 participants enrolled for the development set [7].

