#### External Validation

For assessment of the prediction accuracy of the model, the sample size was calculated based on the assumption that 85% specificity would be the lowest level worth carrying forward because lower values would be considered too low for such a model to be used to make clinical decisions. We focus on specificity, because we are keen for the model to correctly identify the true negatives (and reduce the number of false negatives) considering the risk associated with missing a diagnosis. Based on a 95% CI and precision of 0.05, we aim to recruit at least 1400 patients for model external validation, assuming 87% specificity and a hospitalization rate of 10%.

Assuming a loss to follow-up of 5%-6%, due to possible linkage failure or not recording admission, we aim to recruit at least 2880 participants.

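### The one prespecified sensitivity analysis for missing admissions compares no method with an unnamed method, so it need not vary the missingness assumption that matters

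*SAP article*

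**What the plan says.** All references are to the SAP article.

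- **Missing Data, trigger:** "If model outcome data are missing for >5% of the patients", missing-data methods will be applied. The method for the outcome is not named.
- **Missing Data, sensitivity analysis:** this consists of "comparing the estimated risk obtained without implementing a missing data method and the risk estimated using missing data methods". Its declared aim is to gauge what difference the methods make. The quantity called estimated risk is not defined further.
- **Missing Data, predictors:** predictors with less than 50% missing are imputed by chained equations, with 5 imputations combined by Rubin's rules. Admission enters the imputation model to help impute predictors. Imputing admission itself is not described.
- **Missing Data, mechanism:** the plan will investigate whether data are missing completely at random, at random or not at random, and will compare patients with and without missing data.
- **Software:** miceMNAR is listed among the main packages. No analysis is tied to it.
- **Sample Size, External Validation:** "Assuming a loss to follow-up of 5%-6%, due to possible linkage failure or not recording admission".

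**The concern.** A sensitivity analysis for missing outcomes is informative when it changes the assumption that the data cannot test. Here that assumption is that, given the observed variables, patients with unknown admission status were admitted as often as patients with known status. The planned contrast changes whether a method is used. It does not, as written, change that assumption.

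The plan itself supplies a reason to doubt the assumption. Linkage failure may be unrelated to admission, but an unrecorded admission can occur only in a patient who was admitted. The expected loss of 5%-6% also sits at or just above the 5% trigger, so the analysis may well be run.

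If admissions are lost more often than non-admissions, every predicted risk tends to be too low. That is the unfavourable direction for a tool whose section on internal validation and evaluation wants few false negatives and a green category reserved for patients at very low risk.

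The point concerns only outcomes recognised as missing. How unlinked patients are coded is a separate matter.

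**Working it through.** **1. The plan's own figure.** Development and validation targets: 1317 + 1400 = 2717. Inflating for loss gives 2717/0.95 = 2860, 2717/0.945 = 2876 and 2717/0.94 = 2891; 2717 × 1.06 = 2880.02. The stated total of 2880 fits a loss of 5%-6%. The expected amount of missing outcome data is therefore built into the design. The plan gives no figure for the sensitivity analysis itself.

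**2. Size of the bias, by direct arithmetic.** From the plan: admission rate 10% ("Assuming that 10% of patients diagnosed with COVID-19 will be admitted to hospital") and 6% missing. Assumed: missingness depends only on admission, with odds ratio k. Let p0 and p1 be the probabilities of a missing outcome in non-admitted and admitted patients. Then

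- p1 = k·p0 / (1 + (k − 1)·p0)
- 0.1·p1 + 0.9·p0 = 0.06
- observed risk = 0.1·(1 − p1)/0.94
- admission rate among the missing = 0.1·p1/0.06

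| k | p0 | p1 | Observed risk | Shortfall from 10% (points) | Admission rate among the missing |
|---|---|---|---|---|---|
| 1 | 6.0% | 6.0% | 10.0% | 0 | 10% |
| 3 | 5.1% | 13.9% | 9.2% | 0.8 | 23% |
| 5 | 4.5% | 19.2% | 8.6% | 1.4 | 32% |
| 10 | 3.6% | 27.4% | 7.7% | 2.3 | 46% |

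A simulation with n = 2429 (the iCare count in Results), 8 predictors, 5 imputations and 200 runs per scenario, in which admission was imputed from the model's own predictors, gave mean risks of 9.1%, 8.5% and 7.7% for k = 3, 5 and 10. Complete-case and imputed analyses gave the same values.

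**3. Does the planned comparison show this bias?** A second set of simulations used n = 2429, 5 imputations, 100 to 200 runs and assumed coefficients giving an admission rate of about 8%-10%. The first side was taken as complete cases and the second as imputation under missing at random. Entries are mean predicted risk over all patients.

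| Case | No method | Imputed | True |
|---|---|---|---|
| a. Only outcome missing, at random given predictors | 8.15% | 8.15% | 8.15% |
| b1. Only outcome missing; 20% of admitted and 4.5% of others missing (5.7% overall) | 7.04% | 7.04% | 8.18% |
| b2. As b1, with 50% and 5% missing | 4.70% | 4.71% | 8.15% |
| c. Outcome missingness driven by an outcome-related variable in the imputation model but not in the final model | 9.26% | 10.35% | 10.40% |
| d. One predictor missing in about 33%, related to admission, plus 6% of outcomes missing | 13.25% | 9.82% | 9.90% |
| e. As d, predictor missingness unrelated to admission | 9.90% | 9.82% | 9.93% |

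In case a the crude observed risk still differs: 7.75% against 8.16% after imputation.

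**4. Reading the table.** Cases a and b1 both show perfect agreement. In a there is no bias; in b1 both sides are low by 8.18 − 7.04 = 1.14 points. Cases c and d show clear disagreement although outcomes are not informatively missing once the observed variables are used. Neither agreement nor disagreement tells the reader whether lost admissions have biased the risk.

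**5. What varying the assumption shows.** Take an observed admission rate of 10% and 6% missing. Overall risk = 0.94 × 10% + 0.06 × q, where q is the rate among the missing:

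- q = 10%: 10.0%
- q = 20%: 10.6%
- q = 30%: 11.2%
- q = 50%: 12.4%

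This range is what a reader needs, and the stated comparison does not produce it.

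**The case against.** The strongest reply is that the plan does not fix the method being criticised. It names neither complete-case analysis nor missing-at-random imputation for admission. It commits to examining mechanisms and lists miceMNAR, so a not-at-random method is unspecified rather than excluded. The stated purpose is also modest: to gauge the effect of using the methods, not to test for informative loss. This stands, and it makes the point conditional. It does not remove it. No analysis is attached to miceMNAR, and examining observed data cannot separate missing at random from not at random.

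A reader might infer more: that the two analyses agree by construction, so the check can never fail. The document does not support this. Exact agreement of the fitted models needs the outcome alone to be missing and to be imputed from exactly the final model's predictors. This plan expects missing oxygen saturation, temperature and respiratory rate. It imputes from all retained candidates although backward elimination may later drop some, and it leaves estimated risk undefined. Cases c and d, and the crude risks in case a, show that the two sides can differ, and in c and d the comparison exposes real complete-case bias.

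The magnitudes also rest on odds of missingness that have no source in the document, and linkage failure need not depend on admission. That stands too, which is why the size is given as a range.

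**Conclusion.** The point holds in conditional form. The only sensitivity analysis specified for missing admissions contrasts using no method with using an unnamed one. If that method assumes missing at random, the contrast leaves the critical assumption untouched: agreement does not reassure, and disagreement does not diagnose informative loss.

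At 6% missing and a true rate of 10%, odds of missingness 3 to 10 times higher in admitted patients understate mean risk by about 1 to 2 percentage points (0.8 to 2.3 in the arithmetic above). The bias is zero if missingness is unrelated to admission. The 10% rate and the 5%-6% loss are the plan's; the odds ratios, predictor effects and simulated missingness patterns are assumptions.

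It does not follow that the trial will report missing outcomes as harmless, or that the plan rules out a not-at-random analysis. The document shows only that none is specified. This should be corrected before analysis; it does not invalidate the model-building strategy.

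**What to change.** In Missing Data:

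1. Name the method for missing admission and define the estimated risk being compared (crude rate or mean model-predicted risk, and in which patients).
2. Keep the planned with-and-without comparison, labelled as descriptive.
3. Add a prespecified shift (delta) analysis: impute missing admissions with the log-odds of admission shifted from the missing-at-random model over a stated range, for example odds ratios 1, 2, 3, 5 and 10. Where missingness depends only on admission, this odds ratio equals k above, so the range can be judged against plausible rates of unrecorded admission.
4. At each value report mean risk, calibration, sensitivity and green-group risk, and state the value at which conclusions change.
5. Say whether miceMNAR is to be used for this purpose.

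The cost is a paragraph of SAP text and a few reruns of the imputation. No extra data are needed. The drawback is a wider reported range.

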#### Objective 1 (Primary Objective): Development, Internal Validation, and Identification of Clinical Cut-Off Points of the RECAP-V1 Model

The primary objective of the study is to develop a predictive model based on a logistic regression of the predictive parameters using data from the iCare system. The model will be internally validated by bootstrapping the dataset. Following the internal validation, two cut-off points will be used as separators for red, amber, and green risk of a particular outcome with associated interval likelihood ratios (LRs).

A probabilistic risk prediction based on a multivariable logistic regression model, including the variables in Figure 1 as factors, will be performed on the patients from the iCare dataset, with continuous predictors being treated as fractional polynomials to reflect the potential nonlinearity of the variables. The model will allow estimation of the likelihood of a particular patient being admitted to hospital within 28 days of a COVID-19 diagnosis (primary patient outcome). Some of the variables will be checked for independence from each other by including interaction terms in the model. We will test interactions between BMI and respiratory rate (or shortness of breath if respiratory rate is not collected), age and respiratory rate (or shortness of breath), and coronary heart disease and respiratory rate (or shortness of breath).

The significance of each factor in the list of predictor parameters from Figure 1 will be investigated using a backward elimination regression model, where a multivariable regression model is constructed in the first instance including all of the parameters from the list in Figure 1 and their performance assessed to check for significance. Subsequently, a model using only the predictor factors that were found to be statistically significant (*P*<.05) for the prediction of results will be run.

The final model will then be used to estimate the predicted risk for each patient in the iCare dataset. Based on this continuous risk, the specificity and the sensitivity will be calculated based on the formulas shown in Figure 2. All analyses will be completed after the last patient’s final follow-up.

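### Five imputations are fixed whatever the missingness, so keeping a predictor near P=.05 depends on the random seed; the imputation model as listed also omits the planned respiratory-rate interactions

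*SAP article*

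**What the plan says.** Missing Data sets a ceiling for imputation: "If the degree of missingness is above 50% for any predictor variable, then that predictor variable will be excluded from the model". Below it, "If the degree of missingness is less than 50%, the data will be imputed using multiple imputation chain equations". The number of imputations is a single constant: "A total of 5 imputations will be performed and aggregated" by Rubin's rules. The same section names oxygen saturation, temperature and respiratory rate as fields likely to be missing and particularly important for the outcome. Exploratory Analyses repeats that these three are at high risk of missingness.

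On the imputation model, Missing Data says "all of the predictor variables (with less than 50% missing data) will be included in the imputation model", along with complete variables and the outcome. The form is given as "We will use linear regression for continuous variables (normally distributed or transformed), and logit or ordinal logit regression for categorical variables". No product or polynomial terms are mentioned. The same methods apply to all datasets.

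Objective 1 treats continuous predictors as fractional polynomials. It plans three interactions that all involve respiratory rate ("We will test interactions between BMI and respiratory rate", then age and coronary heart disease with respiratory rate), with shortness of breath as the substitute if respiratory rate is not collected. It uses backward elimination and refits with predictors significant at P<.05.

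**The concern.** There are two separate issues.

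**Number of imputations.** Pooled estimates and P values carry Monte Carlo error that shrinks only as the number of imputations m grows. When a hard P<.05 rule decides which predictors stay, that error can become a different set of predictors. Two analysts following the plan exactly, with different seeds, could then publish different versions of RECAP-V1. The introduction gives prevention of data-driven interpretation as the reason for prespecifying, and seed-dependent selection works against that aim.

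**Compatibility.** If respiratory rate is imputed from a model without interactions, the imputed values contain none. Mixing them with observed values pulls the estimated interaction toward zero, so a real interaction may be eliminated because of how the gaps were filled.

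**Working it through.** **Inputs from the SAP.** m=5, imputation up to 50% missing, outcome included in the imputation model (Missing Data); P<.05 selection and three respiratory-rate interactions (Objective 1); 10% admissions and development minimum 1317 (Sample Size); 2429 iCare patients recruited (Results). The plan gives no derivation of m=5, so there is no figure to reproduce.

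**Assumptions not in the SAP.** The FMI values, z=2.3, the simulated effect sizes and the true interaction of 0.30. Selection is taken to use pooled P values.

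**Step 1: efficiency, the usual support for m=5.** Relative efficiency is 1/(1+FMI/m). At FMI 0.5 this is 1/(1+0.5/5) = 1/1.1 = 0.91, so the standard error is √1.1 = 1.049 times its limiting value, 4.9% larger. That loss is small. The Monte Carlo share of the pooled standard error is √[(FMI/m)/(1+FMI/m)] = √(0.1/1.1) = 0.30. A random component of that size matters when the estimate is compared with a cut-off.

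**Step 2: seed dependence of the keep/drop decision.** Scale the total variance at infinite m to 1, with within-imputation variance 1−FMI and between-imputation variance FMI. For each seed, draw the pooled estimate from N(z, FMI/m) and the between-variance estimate B from FMI·χ²(m−1)/(m−1). Then T = (1−FMI) + (1+1/m)B, and the t test uses Rubin's degrees of freedom, (m−1)[1+(1−FMI)/((1+1/m)B)]². Share of seeds with P<.05 at z=2.3:

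| FMI | m=5 | m=20 | m=50 |
|---|---|---|---|
| 0.5 | 59% | 89% | 99% |
| 0.3 | 74% | 97% | >99% |
| 0.2 | 84% | >99% | >99% |
| 0.1 | 96% | >99% | >99% |

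At FMI 0.5 the 95% range of the P value over seeds is .001 to .20 with m=5 and .010 to .047 with m=50. At FMI 0.5 and m=5, a predictor with z=4 is kept in 99% of seeds, z=5 in 100% and z=1 in under 1%.

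**Step 3: the same question with simulated patients.** One borderline predictor, about 10% events, 60 datasets with 200 re-imputations each. Chance that two seeds disagree on P<.05:

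| n | Missing | m=5 | m=50 |
|---|---|---|---|
| 1317 | 20% | 9.5% | 1.3% |
| 1317 | 35% | 20.5% | 6.3% |
| 1317 | 50% | 18.0% | 4.3% |
| 2429 | 20% | 12.3% | 2.9% |
| 2429 | 35% | 15.3% | 7.9% |
| 2429 | 50% | 22.0% | 6.1% |

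**Step 4: how many imputations.** The rule m = 1+0.5(FMI/CV)², with a 5% coefficient of variation for the standard error, gives 1+0.5(0.2/0.05)² = 9 at FMI 0.2, 19 at 0.3, 33 at 0.4 and 51 at 0.5. At 10% CV and FMI 0.5 it gives 13.5, so about 14.

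**Step 5: interaction.** True age by respiratory-rate coefficient 0.30, respiratory rate missing completely at random, linear imputation from the other covariates and the outcome. Full data returned about 0.30.

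| Missing | No product terms, n=1317 | No product terms, n=20000 | With outcome-by-covariate terms, n=1317 | With outcome-by-covariate terms, n=20000 |
|---|---|---|---|---|
| 20% | 0.252 | 0.250 | 0.281 | 0.277 |
| 35% | 0.219 | 0.217 | 0.263 | 0.263 |
| 50% | 0.176 | 0.178 | 0.233 | 0.249 |

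The loss is the same at n=20000, so it is systematic. Outcome-by-covariate terms cut the bias at 50% from about −40% to between −22% (0.233/0.297) and −16% (0.249/0.298), which is only part of it. When missingness depended on observed covariates, the estimates without product terms were 0.22-0.23 at 20% and 0.16 at 50%. At n=2429 and 50% missing completely at random, a run with no correlated auxiliary variable gave 0.145. One auxiliary correlated at 0.5 gave 0.18, and one at 0.7 gave 0.21. Taken together, the runs with values missing completely at random centre on 0.25-0.26 at 20% and 0.16-0.20 at 50%.

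**The case against.** The strongest reply has four parts.

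- **Fifty percent is a ceiling, and FMI is not the missing fraction.** Actual missingness is not reported, and FMI falls when correlated variables enter the imputation model, as they do here. This stands. At FMI 0.1 five imputations are nearly adequate (96% kept). The problem grows with missingness, and the plan's m does not respond to it.
- **Only near-threshold predictors are affected.** A reader might infer that the seed would decide the fate of the very predictors the plan calls important. The documents do not support that. If oxygen saturation, temperature and respiratory rate predict as strongly as expected, they are kept under almost any seed (99% at z=4). What remains exposed is any incomplete predictor or interaction of modest strength.
- **The form of the imputation model is inferred.** A reader might take the SAP to prescribe main effects only. Missing Data lists variables and regression types; it does not expressly exclude product or polynomial terms, and a journal article may leave such detail to a fuller plan. The interaction point is therefore conditional.
- **No invalid tests are shown.** A reader might infer false-positive interactions or biased fractional-polynomial curves. With no true interaction, a check rejected in 2% of datasets at 20% missing and 0.1% at 50%, against a nominal 5%. The tests become conservative and the cost is power. Bias in the fractional-polynomial terms was not computed and is not claimed.

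The plan's comparison of observed with imputed values addresses neither issue, and machine-learning imputation is exploratory and leaves the primary model unchanged.

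**Conclusion.** The point holds in two parts of unequal certainty.

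The first is documented. A fixed m=5 alongside imputation up to 50% missing and P<.05 selection makes the choice of borderline predictors seed-dependent. The size runs from slight at FMI 0.1 to near a coin toss at 0.5, assuming z=2.3 and pooled P values. The harm is a selection that cannot be reproduced; the efficiency loss is small.

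The second is conditional on the imputation model being built from only the terms listed. A true interaction with imputed respiratory rate would then be attenuated, by roughly a sixth at 20% missing and by about a third to nearly a half at 50%, with loss of power. This rests on an assumed coefficient of 0.30 and on an interaction existing at all.

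Neither part shows that RECAP-V1 as a whole would be unstable. The change should still be made, because it is cheap and the plan itself anticipates missingness in these fields.

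**What to change.** In Missing Data, replace the fixed five with a number at least equal to the percentage of incomplete records (about 50 when a predictor is near the 50% ceiling), and fix and report the random seed. A fixed seed alone makes the result repeatable without making it stable, so both are needed. A floor of 50 at low missingness is unnecessary.

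In the description of the imputation model, state that it will be compatible with the analysis model, including the three respiratory-rate interactions and the fractional-polynomial terms. Substantive-model-compatible chained equations are preferable, since outcome-by-covariate product terms remove only part of the bias at high missingness. If such terms were always intended, one sentence saying so settles that part. Predictive mean matching is optional.

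The cost is computing time and SAP wording. No new data are needed.
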